#### T0, T1, T2, T3, T4, and 1-year follow-up measures T5 (girls)

##### Self-reported negative affect: co-rumination

The original measure [9] to assess co-rumination included 27 items that measure the extent to which youth typically co-ruminate with same-sex friends. Nine content areas are covered, including (a) frequently discussing problems, (b) discussing problems rather than doing other activities, (c) friend encouraging discussion of problems, (d) target child encouraging friend to discuss problems, (e) discussing repetitively the same problem, (f) speculating about cause of problems, (g) speculating about consequence of problems, (h) trying to understand parts of problems, and (i) focusing on negative affective feelings. The items focus on assessing a more extreme form of discussing problems beyond mere self-disclosure.

For the present study, 9 items (1 for each of the topic areas) will be used to assess co-rumination at T0, T1, T2, T3, T4, and T5 1-year follow-up (Co-rumination Questionnaire-short; CRQ-short). These items include: “We talk about problems that my friend or I are having almost every time we see each other”, “When we see each other, if one of us has a problem, we will talk about the problem even if we had planned to do something else together,” “When my friend has a problem, I always try really hard to keep my friend talking about it.,” “When I have a problem, my friend always tries to get me to tell every detail about what happened,” “When we talk about a problem that one of us has, we’ll talk about every part of the problem over and over.,” “When we talk about a problem that one of us has, we talk about all of the reasons why the problem might have happened.,” “When we talk about a problem that one of us has, we try to figure out every one of the bad things that might happen because of the problem.,” “When we talk about a problem that one of us has, we spend a lot of time trying to figure out parts of the problem that we can’t understand.,” and “When we talk about a problem that one of us has, we talk a lot about how bad the person with the problem feels.”

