#### T0 and T4 measures (girls)

##### Observed regulation of negative affect: co-rumination

Co-rumination and the topic of problems (interpersonal problems/non-interpersonal problems) will be observed with the Dutch version of the standardized Problem Talk Task (PTT; [22, 67]. Participation of girls will take place online using the protected Teams-environment of Rotterdam University of Applied Sciences. Both girls will receive links to the Teams-observations via email. The observations will be recorded via Teams. The PTT will start with a short warm-up task. Girls will be asked to plan a party together and to discuss the guest lists, the location, the theme of the party, etc. After the warm-up task, dyads will be told that they will have 16 min to discuss problems or worries they want to share and that are allowed to discuss anything about the problems and/or worries. They will be asked to discuss each friend’s problem and will be told that they are allowed to spend as much time as they want to on each person’s problem/worries. They will be told that, if they finish talking about problems, they could talk about something else.

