#### Observations co-rumination T0 and T4

For a detailed description of the PTT, please see the section “Primary outcome variables.” The duration of the PTT is 30 min. The video recordings will be conducted by trained research assistants through Teams (students Developmental Psychopathology of the Vrije Universiteit Amsterdam) and will be supervised by both PhD students.

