### Statistical methods for primary and secondary outcomes

Hypothesis 1 “Girls in the intervention group will have a greater reduction in co-rumination about distress and difficult emotions and feelings, (and thereby) internalizing symptoms and negative affect during the intervention period, immediately after the intervention period and after 1-year follow-up, relative to girls in the control condition” will be tested via (a) a multi-level parallel process, dual latent growth curve model (with co-rumination measured via self-report) and (b) a multi-level autoregressive cross-lagged model (with co-rumination measured via observation [100, 101]).

For analysis (a) with co-rumination measured via self-report (T0 to 1-year follow-up T5), we will use multi-level parallel process, dual latent growth curve (LGM) models, with intervention arm as the exogenous predictor variable, growth rate of co-rumination as the mediating variable, and growth rate of internalizing symptoms and negative affect as (correlated) outcome variables. See Fig. S3 for a simplified visual representation of this model.

For analysis (b) with co-rumination measured via observations (T0 and T4), we will use a multi-level autoregressive crossed-lagged model, with intervention arm as the exogenous predictor variable (relative change from T0 to T4 in) co-rumination as the mediating variable and (relative change from T0 to T4 in) internalizing symptoms and negative affect as (correlated) outcome variables. See Fig. S4 for a simplified visual representation of this model.

Hypothesis 2 “Girls in the intervention group will have (a) a later onset of depressive symptoms or a later onset of depressive disorder and (b) less dyadic depression contagion during the intervention period, immediately after the intervention period and after 1-year follow-up, relative to girls in the control condition” will be tested using discrete-time survival analysis [102] and via actor-partner interdependence modeling [103], respectively.

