Hypothesis 8 “Girls in the intervention group will demonstrate a change in subjects discussed: girls will demonstrate less problem talk about interpersonal problems and shorter periods of interpersonal problem talk immediately after the intervention period and after 1-year follow-up, relative to girls in the control condition” will be tested using Latent Transition Analysis (LTA). Via LTA it can be tested whether girls transition from one class (e.g., a class consisting of girls who engage a lot in interpersonal problem talk; class 1) to another class (e.g., a class consisting of girls who do not engage a lot in interpersonal problem talk; class 2) over time (i.e., between T0 and T4). Via multi-group testing we will investigate whether the probability of changing from class 1 to class 2 is higher for girls in the intervention arm compared to girls in the control arm.

Hypothesis 9 “The hypothesized intervention effects on (the onset) of depression and anxiety symptoms or disorders and depression contagion and anxiety contagion are differently related to changes in interpersonal components of the conversations between girls” will be tested via a joint LTA and DTSA model. First, classes of girls who do and who do not change in their amount and period of interpersonal subjects discussed will be identified via an LTA. Next, it will be investigated whether the resulting classes retrieved from the LTA (i.e., probability of class-membership for the identified transition classes) is a mediator between the intervention effect and the DTSA model of the onset of depression and anxiety symptoms or disorders.

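### Hypothesis 9 calls the T0-to-T4 talk class a mediator of onset, yet four of the five post-baseline onset occasions fall at or before T4, so reverse influence can pass as mediation

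*Protocol article*

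**What the plan says.** All references are to the protocol article.

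- **Mediator.** Under Statistical methods for primary and secondary outcomes, Hypothesis 9 is tested with a joint latent transition analysis (LTA) and discrete-time survival analysis (DTSA). The question put to that model is whether a girl's LTA transition class "is a mediator between the intervention effect and the DTSA model of the onset of depression and anxiety symptoms or disorders".
- **Mediator window.** Hypothesis 8, which introduces the LTA, defines the transition "over time (i.e., between T0 and T4". The Problem Talk Task that supplies the conversation data is listed under "T0 and T4 measures (girls", and Study procedures repeats this under "Observations co-rumination T0 and T4".
- **Outcome occasions.** The CDI-2 for depression and the RCADS generalized anxiety subscale are both listed under "T0, T1, T2, T3, T4, and 1-year follow-up measures T5 (girls".
- **Onset window.** As restated in the data analysis plan, Hypothesis 2 on depression ends with "less dyadic depression contagion during the intervention period, immediately after the intervention period and after 1-year follow-up". Hypothesis 3 on anxiety covers the same three periods.

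The Hypothesis 9 text does not restrict onset to the time after T4, does not lag the mediator, and does not describe the analysis as associational.

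**The concern.** A mediator has to come before the outcome that it is said to carry. Here the transition class is complete only at T4, while the onset model as described can take events at T1, T2, T3 and T4. A girl who crosses the depression threshold at T2, and for that reason still dwells on interpersonal problems in the T4 conversation, would add to the association between class and onset. The model would read this as talk leading to onset. Randomisation gives no protection, because it covers the effect of arm and not the path from mediator to outcome.

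The article itself makes the reverse path plausible. Its Background describes friends with internalizing symptoms as turning conversations towards themselves and seeking much reassurance. Its safety section has parents informed, and advised to seek help, when a CDI-2 or RCADS score passes a cut-off at any wave. If onset is defined near those cut-offs (an assumption), an early onset sets off a response before the T4 conversation.

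At stake is the mechanism claim. The article names mechanisms of change as part of the trial's objective. A positive Hypothesis 9 would be read as showing that changing interpersonal talk delays depression or anxiety.

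**Working it through.** The plan gives no figure on this point, so there is none to reproduce. The check has four steps.

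**1. Order of occasions.** Mediator: T0 and T4. Onset: T1, T2, T3, T4, T5. Occasions at or before T4: 4 of 5. Only T5 follows the mediator.

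**2. Share of onset events at or before T4.** No onset rate is stated, so the five-wave cumulative incidence c is assumed to lie between 5% and 50%.

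*Equal hazard h per wave:* share = [1 − (1 − h)^4] / [1 − (1 − h)^5]. With h = 0.05: (1 − 0.8145) / (1 − 0.7738) = 0.185 / 0.226 = 0.82. Over c = 5% to 50% the share is 0.80 to 0.85.

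*Constant hazard per month:* share = [1 − (1 − c)^(a/(a+b))] / c, where a is months from T0 to T4 and b is months from T4 to T5. From Timeline of the intervention and measures, a = 11 for cohort 1 (October 2023 to September 2024) and a = 9 for cohort 2 (October 2024 to July 2025). T5 is given as July 2025 to 2026, which is read as b = 10 to 12.

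| c | cohort 1, b = 10 | cohort 1, b = 12 | cohort 2, b = 12 |
|---|---|---|---|
| 5% | 0.53 | 0.49 | 0.44 |
| 30% | 0.57 | 0.52 | 0.47 |
| 50% | 0.61 | 0.56 | 0.51 |

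Because T4 to T5 is about as long as T0 to T4, the share is roughly half on this scale.

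**3. What reverse influence could do (illustration only).** Two simulations used 320 girls. Talk class had no effect on onset, arm changed class, and onset by T4 lowered the odds of being in the low-talk class. Class was entered as a fixed covariate in a discrete-time logistic model.

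| | Simulation A | Simulation B |
|---|---|---|
| Onset | 5% or 8% per wave | 30% cumulative, by month or by wave |
| Odds ratio, arm on class | 2.0 or 2.7 | e^0.8 = 2.2 |
| Odds ratio, onset on low-talk class | 1/2.2 or 1/3.3 | 0.50 or 0.37 |
| Test | product interval, hypothesised direction (nominal 2.5%) | both paths significant at two-sided 5% |
| False mediation, onsets T1 to T5 | 53% to 96% | 34% to 83% |
| False mediation, T5 onsets only | 1% to 4% | 3% to 5% |
| No reverse effect, onsets T1 to T5 | 1% to 3% | 4% to 6% |

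In B, the apparent odds ratio for the null mediator was 0.48 to 0.69 with all onsets and 0.99 to 1.01 with T5 onsets only. Both simulations ignore dyad clustering and treat class as known.

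**4. Events left after T4.** Expected T5 onsets = 320 × (1 − h)^4 × h. At h = 0.05: 320 × 0.8145 × 0.05 = 13.0. At h = 0.08: 320 × 0.7164 × 0.08 = 18.3. These counts take all 320 girls as at risk at T0 and assume no dropout.

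**The case against.** - **The onset window is inferred.** Hypothesis 9 does not list the waves in its survival model. For depression the article is not uniform: the hypotheses in the Background omit the programme period, and the data analysis plan includes it. The article says that it reports principal features only and refers to a SAP, which is not shown and may set the risk set or a lag. This tempers certainty. It does not remove the point, because the article itself fixes the mediator, its window and its causal role. T4 onset is within both versions and coincides with the mediator.
- **Most onsets need not come first.** A reader might infer from four occasions in five that most onset events precede the mediator. The documents do not support that: they give no onset rates, and the wave spacing is very unequal. The flaw needs no majority.
- **The error rates are not the trial's.** A reader might take 34% to 96% as the false-positive rate of the planned test. The reverse and programme effects are assumed. The plan assigns bootstrap testing of indirect effects to Hypotheses 1 and 5 and names no indirect-effect test for Hypothesis 9. Nor does the text show that onset will alter talk, only that it could.
- **Part of the wording is associational.** Hypothesis 9 itself speaks of effects being differently related to changes in conversation. The analysis description that follows nevertheless says mediator.
- **The remedy is weak.** With 13 to 18 events, low rejection in the T5-only analysis may partly reflect low power. Selecting girls who are onset-free at T4 conditions on a post-randomisation state. This stands, and it has to be disclosed.
- **Importance.** Hypothesis 9 is explanatory and is absent from the eight hypotheses in the Background. No main arm comparison depends on it.

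**Conclusion.** The concern holds as a matter of time order. The mediator is known only at T4, and four of the five post-baseline onset occasions are at or before it. As written, the plan allows an effect of onset on conversation to be reported as mediation.

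The size cannot be fixed from the documents. The share of events at or before T4 is roughly half under a constant monthly hazard and about 80% under an equal hazard per wave. The simulated rates show that the distortion can be large if reverse influence is of the assumed strength, and that it disappears if there is none. The finding rests on the onset model using the programme-period waves, which the measurement schedule and the restated Hypotheses 2 and 3 indicate, and on reverse influence being possible. It bears on what may be claimed about mechanism and leaves the comparison of arms untouched. The change is worth making because it is cheap.

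**What to change.** In Hypothesis 9, in the data analysis plan and in the SAP:

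1. State that the association of the T0-to-T4 transition class with onset over T1 to T5 is descriptive and is not evidence of mediation.
2. Confine any mediation statement to onset after T4 among girls without onset by T4 (a landmark at T4), with arm and transition class in the model.
3. Keep adjustment for the T4 symptom score as a sensitivity analysis, since so few events will not support many terms.
4. Disclose the limits of the landmark analysis: few events (about 13 to 18 of 320 girls at an assumed hazard of 5% to 8% per wave), low power, an arm contrast that is no longer fully randomised because it conditions on the state at T4, and no information on onset during the programme.

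The cost is wording only, with no new data. The price is that Hypothesis 9 may end without a usable mediation result. If the team judges the landmark analysis too thin, step 1 alone, with no mediation statement, is sufficient.

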## Methods/design

### Study design

This paper used the SPIRIT reporting guidelines [60]. The aim of the HFPM cRCT is to evaluate the effectiveness of the school-based targeted mindfulness and psychoeducation blended prevention program HFPM, delivered by trained and experienced mindfulness health professionals, compared with CAU in which girls will receive care-as-usual. The HFPM is a cRCT with two arms: (1) an intervention condition in which 80 girls’ friendship dyads will receive the HFPM program, and (2) a control condition in which 80 girls’ friendship dyads will receive CAU. To prevent contamination across the two trial arms, friendship dyads will be the unit of randomization (see “Randomization, blinding, and treatment allocation”).

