### Sample size calculation

Multi-level models are used with individuals nested in dyads. With a clinical relevant effect size, that is, a difference of 1 *SD* (i.e., Cohen’s *d* = 1) between the control and intervention group where high-risk girls (*M* + 1 *SD*) score on average similar to non-high-risk girls on co-rumination (*M*) after the intervention, and a small to moderate effect association between co-rumination and internalizing problems (Cohen’s *d* = 0.50; [15]), which will result in a possible reduction of depressive feelings with 0.50 *SD*, and an ICC of depressive feelings within dyads of 0.20, 80 dyads (40 control, 40 intervention) will be required (Optimal Design; [62]). However, we will aim to oversample to a maximum of 160 dyads in order to identify smaller effects (Cohen’s *d* = 0.35) that are potentially relevant for theory development, as well as our hypothesized mediating and moderating factors as described in the “Data analysis plan” section.

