### Care-as-usual (CAU)

In the control condition, girls receive unchanged CAU including teaching practices they are already exposed to in their current schools. No other classroom-based mindfulness interventions will be implemented during the intervention period of the cRCT.

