### Train the trainers to deliver the program

The training sessions will be delivered in academic year 2023/2024 (cohort 1) and 2024/2025 (cohort 2) by mindfulness-trained staff members (i.e., PI, PhD students and external staff members). All HFPM trainers have followed an 8-week Mindfulness for Life course at the Oxford Mindfulness Foundation in academic year 2021/2022 or 2022/2023 (seven 2-h sessions per week and one whole day session, supported by a course booklet and several digital guided mindfulness practices to facilitate mindfulness practice during and after the 8-week course). Furthermore, they will all have an established mindfulness practice of more than 6 months before the prevention program starts.

Between October 2023 and January 2024, all trainers will attend a 4-day training program to learn how to deliver the program to the friendship dyads. To maximize fidelity, all trainers have to reach adequate adherence and competence standards before they start teaching trial dyads. This will be conducted through roleplay. During program implementation, all trainers will receive weekly supervision on competence and adherence by the PI [name], who also finalized the Mindfulness Frame by Frame course (Oxford Mindfulness Foundation) and the Teacher Training course “Dot-b” (MISP). During the cRCT, competence and adherence will be monitored. Following study procedures of the MYRIAD mindfulness trial regarding the use of the MBI: TAC [63, 64], an independent rater ([name]) and PI [name] will weekly randomly select a subset of 10% of the videotapes for fidelity monitoring using the MBI:TAC instrument.

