Specifically, discrete-time survival analysis (DTSA) will be used to investigate whether girls in the intervention group have a later onset of depression symptoms or disorder compared to girls in the control arm. Note that this hypothesis focuses on individual rather than dyadic outcomes. To adjust for individuals clustered within dyads, we will adjust the standard errors using a sandwich estimator [104]. Furthermore, a prospective change, Actor-Partner Interdependence Model (APIM) will be used to investigate whether dyads in the intervention condition will experience less dyadic depression contagion compared to dyads in the control arm from T0 to 1-year after follow-up. We will use multi-group comparisons to test whether contagion effects are less strong in the intervention arm compared to the control arm.

Hypothesis 3 “Girls in the intervention group will demonstrate (a) less anxiety problem talk and will have a (b) later onset of anxiety symptoms or a later onset of anxiety disorder and (c) less dyadic anxiety contagion during the intervention period, immediately after the intervention period, and after 1-year follow-up, relative to girls in the control condition” will be tested using multi-level LGM, DTSAs, and multi-group APIM, respectively.

Specifically, a multi-level LGM with intervention arm as the exogenous predictor variable and growth rate of anxiety problem talk as the outcome variable will be used to test whether girls in the intervention arm demonstrate less anxiety problem talk compared to girls in the control arm. Furthermore, DTSAs of anxiety symptom onset and anxiety disorder onset with intervention condition as an exogenous predictor will be used to test whether girls in the intervention group have a later onset of anxiety symptoms or disorder compared to girls in the control arm. Lastly, a multi-group (i.e., intervention versus control condition) APIM will be used to investigate whether dyads in the intervention condition will experience less anxiety contagion compared to dyads in the control arm from T0 to 1-year after follow-up.

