All analyses will be conducted in structural equation modeling program Mplus (v 8.7 or higher; [106]). Model fit will be determined using the comparative fit index (CFI; critical value ≥ 0.95), the root mean square error of approximation (RMSEA; critical value ≤ 0.06), and the standardized root mean square residual (SRMR; critical value < . 08; [107]). When appropriate, standard errors will be adjusted for clustering of dyads within schools using a sandwich estimator [104]. For hypotheses that include mediation analysis (hypothesis 1 and 5), we will use 10,000 bootstrap resamples with replacement and bias-corrected 95% confidence intervals to test these indirect effects [108]. When appropriate, differences in (indirect) pathways between the intervention and the control arm will be estimated using the DIFFtest option in Mplus (when using the weighted least squares means and variance adjusted (WLSMV) estimator) or the Satorra Bentler chi-square difference test [109]; when using the maximum likelihood estimator with robust standard errors (MLR) estimator).

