It is also possible that there will be deteriorations in girls’ functioning as a result of *frictions with the dyad friend* during the intervention period. The training program consists of fourteen online meetings in which the dyads participate together. Each dyad has its own trainer who provides training during all meetings. Every meeting the trainers discuss with the dyads how the cooperation with the app and the homework assignments went in the previous practice period. These discussions have a signaling function: trainers will invite the girls to share all their experiences. We assume that girls will share any problems regarding, for example, their motivation and any frictions or disagreements with the trainers (or that these are observable by the trainers based on verbal and non-verbal behavior during the meetings), so that solutions can be found together. If necessary, trainers may also seek general advice with the teacher-mentors. These possible problems, solutions, and results are shared by the trainers during the intervisions, so that trainers can offer uniform advice as much as possible.

The use of the app is monitored at the individual level by the researchers. When girls do not fill in the diary and moodtracker for more than 3 days in a row, the researchers will pass this on to the trainers, because this may indicate motivation problems, whether this is caused by mutual friction or something else. But girls may also be sick, for example, which causes them to lose track of the app for a while. During the next meeting, the trainers will discuss the causes of non-response with the dyads and jointly look for solutions. Together with possible solutions and results, this information will also be shared by the trainers during the intervisions.

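### The sample size and stated analysis leave out trainer clustering in the HFPM arm; if outcomes vary by trainer, standard errors will be too small and d = 0.35 is optimistic

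*Protocol article*

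**What the plan says.** All locations are in the protocol article.

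- **Delivery in the HFPM arm** (adverse-events text on participation in the intervention condition): "The training program consists of fourteen online meetings in which the dyads participate together", and "Each dyad has its own trainer who provides training during all meetings".
- **Who the trainers are** (Train the trainers to deliver the program): "mindfulness-trained staff members (i.e., PI, PhD students and external staff members"). No number is given, and nothing says how dyads are assigned to trainers.
- **Control arm** (Care-as-usual): "In the control condition, girls receive unchanged CAU including teaching practices they are already exposed to in their current schools". There is no counterpart to the trainer.
- **Randomisation** (Study design): "friendship dyads will be the unit of randomization", 80 per arm.
- **Sample size** (Sample size calculation): "Multi-level models are used with individuals nested in dyads", with a within-dyad ICC of 0.20. The article requires 80 dyads for d = 0.50 and plans up to 160 to reach d = 0.35.
- **Analysis** (Statistical methods for primary and secondary outcomes): multi-level models for most outcomes. For the survival models, "To adjust for individuals clustered within dyads, we will adjust the standard errors using a sandwich estimator". Schools enter only conditionally: "standard errors will be adjusted for clustering of dyads within schools using a sandwich estimator".

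Trainer competence and fidelity are recorded, but only as implementation measures.

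**The concern.** This is a partially nested design. HFPM dyads with the same trainer share that trainer's skill and style for fourteen weeks; control dyads share nothing of the kind. Any trainer-to-trainer variation in outcome makes HFPM dyads correlated beyond the dyad level, and in one arm only. A model that stops at the dyad treats them as independent and understates the variance of the HFPM arm mean.

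The school adjustment cannot be counted on to make up for this. It is optional, sessions run online through Teams, and dyads rather than schools are randomised, so one trainer may teach in several schools and one school may hold dyads of both arms.

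Two things are at stake: the false-positive rate of the arm comparison, and the article's justification for doubling the sample from 80 to 160 dyads, which is the smaller effect of d = 0.35.

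**Working it through.** **Inputs from the article.** 80 dyads per arm, two girls per dyad, within-dyad ICC 0.20, d = 0.50 for the required size and d = 0.35 for the planned size.

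**Assumptions.** Two-sided 5% test and 80% power (the article states neither), total variance 1, equal trainer loads. Trainer ICC *r* and number of trainers *k* are not in the article, so a range is shown.

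**1. The article's own figure.** Variance of a dyad mean = 0.20 + 0.80/2 = 0.60. With *J* dyads in total, SE = √(4 × 0.60 / *J*).

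- *J* = 80, d = 0.50: SE = √0.030 = 0.173; power 82.3% (normal), 81.4% (t with *J* − 2 df). The t-based requirement is 78 dyads, which agrees with the stated 80.
- *J* = 160, d = 0.35: SE = √0.015 = 0.1225; power 81.5% (normal), 81.1% (t). The requirement is 156 dyads.

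The stated sizes follow from dyad clustering alone, so at d = 0.35 almost nothing is left over for a trainer effect.

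**2. Trainer effect in the HFPM arm only.** The trainer component is taken out of the 0.20, so the total variance is unchanged:

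Var = [*r*/*k* + (0.60 − *r*)/80] + 0.60/80

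The analysis without a trainer level uses 0.60/80 + 0.60/80 = 0.015. Let *R* be the true variance divided by 0.015. Then:

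- actual type I error = 2 × [1 − Φ(1.96/√*R*)]
- power = Φ(d/√Var − 1.96)

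Example, *r* = 0.05 and *k* = 8: 0.05/8 + 0.55/80 + 0.60/80 = 0.00625 + 0.006875 + 0.0075 = 0.020625. *R* = 1.375 and √*R* = 1.173. Type I error = 2 × [1 − Φ(1.671)] = 9.5%. Power at d = 0.35 = Φ(0.35/0.1436 − 1.96) = Φ(0.477) = 68%.

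| Trainer ICC | Trainers | SE ratio √*R* | Type I error | Power, d = 0.35 | Power, d = 0.50 |
|---|---|---|---|---|---|
| 0 | any | 1.00 | 5.0% | 81.5% | 98.3% |
| any | 80 | 1.00 | 5.0% | 81.5% | 98.3% |
| 0.01 | 20 | 1.01 | 5.3% | 80.6% | 98.1% |
| 0.02 | 10 | 1.06 | 6.4% | 77.2% | 97.2% |
| 0.05 | 20 | 1.06 | 6.5% | 76.9% | 97.1% |
| 0.05 | 8 | 1.17 | 9.5% | 68.3% | 93.6% |
| 0.05 | 4 | 1.34 | 14.3% | 56.9% | 86.2% |
| 0.10 | 8 | 1.32 | 13.8% | 57.9% | 87.0% |
| 0.10 | 4 | 1.61 | 22.3% | 42.8% | 71.9% |

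**3. Few trainers.** The power columns use a normal approximation and are optimistic when *k* is small. A simulation (20,000 trials per cell) compared trainer means with control dyad means using Satterthwaite degrees of freedom.

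- At d = 0.35 and trainer ICC 0.05, power is about 45% with 4 trainers, 63% with 8 and 76% with 20.
- At d = 0.50, power is about 90% (8 trainers, ICC 0.05), 82% (8 trainers, ICC 0.10) and 71% (4 trainers, ICC 0.05).

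**The case against.** **The SAP may deal with it.** The article says that it gives only the main features of the methods and refers to a supplementary SAP, which was not available. A reader might infer that the trial ignores trainers altogether; that cannot be shown, and the point is confined to the article. It does not fall away, because the sample size section itself fixes the clustering and makes the d = 0.35 claim.

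**The pool may not be small.** A reader might infer a handful of trainers from the roles listed. The article gives no number, and external staff is an open category. Well below 80 is still a fair inference. Every trainer needs an eight-week course, more than six months of established practice, a four-day programme and weekly supervision by the PI, and the recruitment and coding sections speak of two PhD students.

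**Trainer variance may be slight.** Sessions are manualised, trainers must meet competence standards before they start, and they share solutions so that advice is uniform. These steps should lower the trainer ICC, so it cannot be said outright that the intervals are too narrow. They do not show that the ICC is zero, and the plan studies fidelity and quality because delivery may affect outcomes.

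**The trial is sized on d = 0.50.** This largely stands: power there with 160 dyads stays at about 80% or more except with very few trainers or a large trainer ICC. It does not answer the type I error.

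**Schools may absorb it.** If trainers were assigned by school, the school adjustment would take up some of the effect. Assignment is not described.

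**The check is a proxy.** The planned analyses are mostly growth models over six waves, not one comparison of dyad means. The percentages are therefore indicative; the direction carries over.

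**Conclusion.** The point holds in conditional form. The article establishes a trainer cluster in one arm only, and no trainer level in either its sample size or its stated analysis. Given a positive trainer ICC and trainers who teach several dyads each, the standard error of the arm effect will be too small. The article supplies neither figure, so the size runs from negligible (type I error 5.3%, ICC 0.01 with 20 trainers) to serious (22.3%, ICC 0.10 with 4 trainers). In the middle of the range, ICC 0.05 with 8 trainers, a nominal 5% test runs at about 9.5% and power at d = 0.35 is 68% rather than 81.5%. The detectable effect of d = 0.35 is the claim most exposed. The point is worth acting on because the correction is cheap, but it does not show that the trial is underpowered for d = 0.50.

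**What to change.** 1. Link a trainer ID to each HFPM dyad from the digital forms that trainers already complete after every session. State the number of trainers and how dyads are assigned to them.
2. Estimate the arm effect on self-reported co-rumination and CDI-2 with a partially nested model: a random trainer effect in the HFPM arm only, none in the control arm, and small-sample degrees of freedom. If the Mplus structural models cannot carry this level, pre-specify it as a sensitivity analysis in a mixed model. A sandwich estimator clustered on trainer is not a good substitute, since with few trainers it is itself biased downwards.
3. Restate the detectable effect in the sample size section over a range of trainer ICCs, using the actual number of trainers. Show power at d = 0.50 beside d = 0.35.

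If the SAP already specifies the second item, a sentence in the article and the restated detectable effect are enough.

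The cost is some analysis-plan wording, one extra variance component and a data link. The downside is somewhat wider intervals and a less favourable stated detectable effect. No additional girls and no change in delivery are needed.
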